## **S1 Protocol. Study protocol**

This study protocol includes additional, related, multidisciplinary studies that were not part of the present epidemiologic core activity. These studies focus on the water quality, quantity and household economics benefits associated with continuous water supply, and their details are described elsewhere [15, 31, 32].

31. Kumpel E. Water Quality and Quantity in Intermittent and Continuous Piped Water Supplies in Hubli-Dharwad, India. Doctoral Dissertation, University of California, Berkeley. 2013.

We made the following changes to this protocol after the protocol was filed but before data collection commenced:

- 1) We added bloody dysentery (blood/mucus in stool), typhoid fever, hepatitis, cholera and <2 child deaths as additional secondary outcomes, in addition to diarrhea (primary outcome) and highly credible gastrointestinal illness as stated in the protocol.
- 2) We did not conduct measurements of child height and upper arm and head circumference due to logistical constraints. For the same reason, we conducted the weight measurements at the last visit only (as opposed to the first and last visits to the households as stated in the protocol).
- 3) Instead of propensity score matching, we used a genetic matching algorithm as a superior alternative to match continuous supply wards to intermittent supply wards.
- 4) Instead of contacting every third house from a selected landmark to assess eligibility for enrollment, we contacted every household as the inclusion criterion of having an <5 child living in the household allowed sufficient geographic spread of enrolled households within the selected study areas.
- 5) We omitted the inclusion criterion of having lived in the area since the onset of continuous delivery. It was typical for families in our study area to relocate often – limiting the study population to households that remained in the same neighborhood would thus have captured a non-representative population.
- 6) Instead of excluding households on the immediate continuous-intermittent boundary, we enrolled them and conducted a sensitivity analysis by conducting our data analysis with and without data from these households.

The original protocol was reviewed and approved by the UC Berkeley Institutional Review Board on 06/10/2010, and subsequently amended on 12/08/2010 to make the following changes:

- 1) The original protocol proposed 12 monthly follow-up visits over one year. We reduced this to 4 visits over one year to avoid respondent fatigue. To maintain the same statistical power with fewer visits, we amended the protocol to enroll a larger number of households.
- 2) We received additional funding to assess the association between continuous supply and waterborne illness in two separate socioeconomic strata (low vs. high income households), and amended the protocol to double the number of households enrolled to allow statistical power for hypothesis testing within each stratum.

These two changes increased the sample size from 720 households in the original protocol to 4000 households in the amended protocol. We have included the amended protocol (approved on 12/20/2010) here to reflect the study design that was ultimately carried out.

---

**Protocol Title:** Impact Evaluation for Continuous Water Delivery in Hubli-Dharwad, India  
**Protocol Status:** APPROVED  
**Date Submitted:** 12/08/2010  
**Approval Period:** 12/20/2010-06/07/2011  
**Important Note:** This Print View may not reflect all comments and contingencies for approval. Please check the comments section of the online protocol. Questions that appear to not have been answered may not have been required for this submission. Please see the system application for more details.

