**1. Purpose**

**Provide a brief explanation of the proposed research, including specific study hypothesis, objectives, and rationale.**

**OBJECTIVE:** The objective of the proposed research is to conduct an impact evaluation for a transition from intermittent water supply, in which water is delivered to consumers a few hours per day or a few days per week on a rotating basis throughout a city, to continuous, fully-pressurized piped water supply. The field work will take place in the city of Hubli-Dharwad, Karnataka, India. As part of a World Bank funded pilot project, 10% of households (70,000 residents) in Hubli-Dharwad were upgraded to continuous delivery in 2007-2008 while the remaining residents continue to receive water once every 4-10 days. We propose to assess the water quality, quantity, health and economic impacts of the upgrade by measuring and comparing these parameters in the continuously and intermittently served areas.

**RATIONALE:** Intermittent delivery of water is a common form of water supply in developing countries. Intermittent delivery may lead to contamination of water in the pipelines and in the home during storage; it may also limit the quantity of water available, negatively impacting hygiene practices and forcing consumers to rely on contaminated non-municipal sources. Moreover, households must invest in water storage and treatment mechanisms to cope with intermittent delivery. Cumulatively, intermittent supply poses a health threat from increased levels of gastrointestinal illnesses caused by poor water quality and limited water quantity, and creates an economic burden due to health-related expenditures and coping costs. Delivery of continuous, fully-pressurized piped water could be a sustainable and scalable solution to these problems. Proponents of continuous water delivery argue that it will provide safe water and improved health to all; opponents claim that the health impacts may be minimal in the presence of other dominant disease transmission pathways and that the benefits will bypass the poor.

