## 7. Screening

- a) **Provide criteria for subject inclusion and exclusion. If any inclusion/exclusion criteria are based on gender, race, or ethnicity, explain rationale for restrictions.**

Two inclusion criteria will be applied during the recruitment process: (1) having at least one child under age five living in the household, (2) having lived in the area since the onset of continuous delivery. To prevent spillover effects, which may occur due to water sharing and the infectious nature of diarrhea, households located in the immediate vicinity of the dividing line between the continuous and intermittent supply zones will be excluded from recruitment.

- b) **If prospective subjects will be screened via tests, interviews, etc., prior to entry into the "main" study, explain how, where, when, and by whom screening will be done. NOTE: Consent must be obtained for screening procedures as well as "main" study procedures. As appropriate, either: 1) create a separate "Screening Consent Form;" or 2) include screening information within the consent form for the main study.**

At the first contact, the investigators will ask the subjects whether they are the parent or primary caretaker of at least one child under the age of five and have lived in the study community since the onset of continuous water delivery. Households not meeting these criteria will not be recruited into the study. If the household meets the criteria, the translator will proceed to recruitment followed by informed consent.

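### Dropping the residence criterion leaves movers' exposure history unrecorded in the text shown, which can misclassify weight and under-2 deaths

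*Protocol*

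**What the plan says.** Section 7 (Screening, a) set two inclusion criteria: a child under five in the household, and "having lived in the area since the onset of continuous delivery". Section 1 (Purpose) says that the pilot areas "were upgraded to continuous delivery in 2007-2008".

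The list of changes at the front of the S1 Protocol, made after filing but before data collection, alters this in three relevant places:

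- **Item 5:** "We omitted the inclusion criterion of having lived in the area since the onset of continuous delivery". The reasons are "It was typical for families in our study area to relocate often" and that "limiting the study population to households that remained in the same neighborhood would thus have captured a non-representative population".
- **Item 2:** "we conducted the weight measurements at the last visit only", instead of at the first and last visits.
- **Item 6:** the exclusion of households on the supply boundary is also dropped, but with a sensitivity analysis, "conducting our data analysis with and without data from these households".

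Item 1 adds under-2 child deaths as a secondary outcome, without a recall window, and confirms diarrhoea as primary. Section 9 (Study Procedures, a) says that basic demographics are collected at the first visit for confounder control. Length of residence is not named.

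**The concern.** With item 5 in force, a household's arm is the zone where it lives at enrolment. That is adequate for an outcome that responds to current supply. It is weaker for an outcome that accumulates over a child's life, or that may have happened before the family arrived.

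- **Weight.** Attained weight reflects conditions since birth. The original first-visit measurement would have allowed a within-child change over the study year. With items 2 and 5 together, neither a baseline nor a residence guarantee remains.
- **Under-2 deaths.** A death that occurred before the family moved can be attributed to the supply at the new address.
- **Diarrhoea.** Families who arrived after the upgrade may have chosen the ward partly for its water. Section 6 matches wards because the municipality selected them non-randomly. Ward matching does not address households sorting themselves afterwards.

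The first two problems can occur in either arm, since a family that left a continuous ward for a control ward is also classified by its current zone. At stake are associations closer to no effect than the truth for weight and deaths, and an unexamined selection question for the primary outcome.

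**Working it through.** **1. The plan's own figures.** The head counts in section 5(b) reproduce: 4000 × (1 + 2) = 12,000, and 12,000 + 700 = 12,700. The 80% power (one-sided 5%, two income strata) cannot be reproduced, because baseline prevalence, hypothesised effect and design effect are not given. Assuming 1000 households × 2 children × 0.9 per arm and stratum, prevalence 5–15%, risk ratio 0.70–0.85 and design effect 1–8, power runs from 10% to 99%. The 80% is therefore taken as given below.

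**2. What movers could cost.** Let m be the share of the continuous arm who are movers, and u the mean share of their relevant exposure spent elsewhere under intermittent supply. The unexposed share is f = m × u. Neither m nor u is in the document. For example, m = 20% and u = 50% give f = 10%. A child aged 3 at weighing who arrived one year earlier has u = 2/3.

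For an outcome fully dependent on past exposure, the contrast shrinks by (1 − f). At 80% power the noncentrality is 1.645 + 0.842 = 2.486, so power = Φ(2.486(1 − f) − 1.645), and the sample size needed to restore 80% is multiplied by 1/(1 − f)².

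| f (assumed) | Power | Sample size multiplier |
|---|---|---|
| 5% | 76% | 1.11 |
| 10% | 72% | 1.23 |
| 20% | 64% | 1.56 |
| 30% | 54% | 2.04 |
| 40% | 44% | 2.78 |

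This is an illustration. The document does not state the power for weight or deaths.

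**3. Children born before the upgrade, kept separate.** Assume ages uniform from 0 to 5 at enrolment at 2010.83. The share born before switch-on is (5 − (2010.83 − date))/5: 23% for 2007.0, 43% for 2008.0 and 63% for 2009.0. Starting anywhere from October to December 2010 widens this to about 20–65%. These children were eligible under section 7 as well, which restricted household residence and not birth date. Item 5 did not bring them in.

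Nor were they unexposed for life. At weighing, one year later (2011.83), ages run from 1 to 6, and mean lifetime is proportional to (6² − 1²)/2 = 17.5. For families who never moved, the unexposed share of lifetime is:

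- switch-on 2007.0: (1.17²/2)/17.5 = 4%
- switch-on 2009.0: (3.17²/2)/17.5 = 29%

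On a ratio scale, purely to show size, a true 0.80 would appear as 0.04 + 0.96 × 0.80 = 0.81, up to 0.29 + 0.71 × 0.80 = 0.86. This background amount exists with or without item 5; movers add to it.

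**4. Deaths.** A child under two at fall 2010 was born from fall 2008 on, essentially after the upgrade. Pre-upgrade time therefore matters only if recall reaches further back. Time before move-in matters under any window that can precede the move.

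**5. Diarrhoea.** Section 1 defines it as longitudinal prevalence, and section 9 measures it at visits from fall 2010 to fall 2011. A recent arrival in a continuous ward has continuous supply when the outcome is measured, so the calculation in step 2 does not apply directly.

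**The case against.** The strongest reply is that item 5 is a reasoned trade-off. Where relocation is normal, a sample of stayers is unrepresentative, and the study's aim is to compare areas as served. This stands as a reason to enrol movers and to keep them in the main analyses. It is not a reason to leave their exposure history unexamined.

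A second reply is that adjustment for residence, or a sensitivity analysis, may sit in an analysis plan that is not at hand, and that the questionnaire is not shown either. This also stands in part: the absence is established only for the text shown. But the move-in date has to be collected; if it is not asked, no analysis plan can recover it. The same change list does state a replacement analysis for the boundary households.

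A third reply is that no mover share is given and that self-selection is conjecture. Both are true. That limits what can be said about size and direction.

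Two stronger readings are tempting. A reader might infer that dropping the criterion made the 23–63% of children born before the upgrade count as wrongly exposed, turning a ratio of 0.80 into 0.85–0.93. That fails because those children were always eligible and because they were exposed from switch-on. A reader might also infer that the primary diarrhoea comparison is diluted. The concurrent measurement does not support that.

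**Conclusion.** The point holds for outcomes that reflect past exposure: weight and under-2 deaths, neither of them the primary outcome. The document itself says that relocation is common, classifies households by current zone, and in the text shown replaces the residence criterion with nothing. If movers otherwise resemble stayers, the misclassification pulls these associations toward no effect. Another direction would need differential migration, on which there are no data.

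The size cannot be fixed from the document. Power of 76% to 44% for f of 5% to 40% rests on assumed values of f, on the stated 80% power, and on an outcome driven entirely by past exposure. The 4–29% of lifetime before switch-on rests on uniform ages and non-moving families, and is not attributable to item 5.

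For diarrhoea, what remains is possible self-selection of post-upgrade arrivals, of unknown direction. It is worth a sensitivity analysis and no more. The change is worth making, but the primary comparison is not shown to be compromised.

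**What to change.** Keep movers enrolled, and change the following:

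1. Ask each household's move-in date at visit 1, and obtain each continuous ward's switch-on date.
2. State the recall window for under-2 deaths, and count deaths and child-time only after both move-in and switch-on. In the matched control wards, use the same calendar window and the same move-in rule, so that the two arms are counted alike.
3. Keep all children in the main weight and diarrhoea analyses. Add analyses with and without post-upgrade arrivals in both arms, parallel to those for boundary households, and show weight by length of residence.

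Restricting the main weight analysis to children born after switch-on and resident since birth is not advised. It would bring back the selection of stayers that the investigators rejected for a stated reason.

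The cost is one questionnaire item, a request for the switch-on dates, a few re-runs of planned analyses, and fewer deaths counted.

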**\*\*\* Purpose, Background, Collaborative Research \*\*\***

Old CPHS # (for Protocols approved before eProtocol)

**1. Purpose**

**Provide a brief explanation of the proposed research, including specific study hypothesis, objectives, and rationale.**

**OBJECTIVE:** The objective of the proposed research is to conduct an impact evaluation for a transition from intermittent water supply, in which water is delivered to consumers a few hours per day or a few days per week on a rotating basis throughout a city, to continuous, fully-pressurized piped water supply. The field work will take place in the city of Hubli-Dharwad, Karnataka, India. As part of a World Bank funded pilot project, 10% of households (70,000 residents) in Hubli-Dharwad were upgraded to continuous delivery in 2007-2008 while the remaining residents continue to receive water once every 4-10 days. We propose to assess the water quality, quantity, health and economic impacts of the upgrade by measuring and comparing these parameters in the continuously and intermittently served areas.

**RATIONALE:** Intermittent delivery of water is a common form of water supply in developing countries. Intermittent delivery may lead to contamination of water in the pipelines and in the home during storage; it may also limit the quantity of water available, negatively impacting hygiene practices and forcing consumers to rely on contaminated non-municipal sources. Moreover, households must invest in water storage and treatment mechanisms to cope with intermittent delivery. Cumulatively, intermittent supply poses a health threat from increased levels of gastrointestinal illnesses caused by poor water quality and limited water quantity, and creates an economic burden due to health-related expenditures and coping costs. Delivery of continuous, fully-pressurized piped water could be a sustainable and scalable solution to these problems. Proponents of continuous water delivery argue that it will provide safe water and improved health to all; opponents claim that the health impacts may be minimal in the presence of other dominant disease transmission pathways and that the benefits will bypass the poor.

**SPECIFIC HYPOTHESES:** The proposed research will test two specific hypotheses. (1) Upgrading to continuous water supply will lead to improved water quality, increased quantity of water used in the households, and improved water-related behaviors such as hygiene and sanitation practices. (2) Upgrading to continuous supply will lead to improvements in children's health (specifically longitudinal prevalence of diarrhea and highly credible gastrointestinal illness (HCGI) in children under five, and anthropometric measures including weight, height, upper arm and head circumference) as well as reductions in health-related expenditures and coping costs born by households.

---

**Protocol Title:** Impact Evaluation for Continuous Water Delivery in Hubli-Dharwad, India

**Protocol Status:** APPROVED

**Date Submitted:** 12/08/2010

**Approval Period:** 12/20/2010-06/07/2011

**Important Note:** This Print View may not reflect all comments and contingencies for approval. Please check the comments section of the online protocol. Questions that appear to not have been answered may not have been required for this submission. Please see the system application for more details.

## 2. Background

Give relevant background (e.g., summarize previous/current related studies) on condition, procedure, product, etc. under investigation, including citations (attach bibliography in Attachments section) if applicable.

Accessible water, free of contamination from human waste, saves lives and improves productivity and quality of life (Fewtrell et al 2005; Clasen et al 2007). Over half of urban residents in India retrieve water from piped connections (McKenzie and Ray 2009), which meet the UN guidelines of "accessible" and "improved" and are therefore presumed to provide safe drinking water (Coelho et al 2003). However, most piped systems in the developing world operate intermittently, providing water in limited quantities and of questionable quality. Most major Indian cities report water availability to consumers for about four hours per day. Intermittent water delivery exists in an estimated third of urban water supplies in Africa and Latin America, as well as more than half of cities in Asia (WHO/UNICEF 2000).

Intermittent delivery can lead to contamination in pipelines through multiple mechanisms (e.g., intrusion of non-potable water through leaks and cracks, bacterial regrowth) (LeChevallier 2003). Distribution systems in developing countries are especially vulnerable as they are often poorly maintained and intermittent water delivery is common (Lee and Schwab 2005), leading to poor health. There have been no rigorous analyses to our knowledge of the transition from an intermittent to continuous water supply. Although contamination has been shown to occur in intermittent systems (Coelho et al 2003; Tokajian and Hashwa 2003), the exact contamination mechanisms have not been adequately explored, and consistent water quality improvements after conversion to continuous supply have not been documented. Similarly, studies have shown increased risk of gastrointestinal illness after short-term intermittencies in otherwise continuously operated systems (Hunter et al 2005; Nygard et al 2007), but the health implications of having a fully intermittent vs. continuous system have not been documented.

## 3. Collaborative Research

a) If any non-UCB institutions or individuals are engaged in the research, explain here.

The Center for Multidisciplinary Development Research (CMDR) in Hubli-Dharwad will be engaged in the research by providing field staff and assisting with data collection and entry. The SDM College of Engineering in Dharwad will assist with water quality testing.

b) If any non-UCB institutions or individuals are collaborating in the research, complete the table below and attach any relevant IRB approvals in the Attachments section.

**\*\*\* Subject Population \*\*\***

**5. Subject Population**

**a) Describe proposed subject population, stating age range, gender, race, ethnicity, language and literacy.**

The subjects will be selected from among the general population of Hubli-Dharwad, living in the continuous and intermittent water delivery zones. The population of Hubli-Dharwad is a mix of Kannada-speaking Hindus and Hindi/Urdu-speaking Muslims. Participants will be recruited from both ethnic/religious groups. According to the 2001 census, the general literacy rate is 0.71 and 0.73 in Hubli and Dharwad, respectively, and the female literacy rate is 0.65 in Hubli and 0.68 in Dharwad. Both literate and illiterate subjects will be recruited into the study. Participants will be households with children under the age of five.

**b) State total number of subjects planned for the study and how many must be recruited to obtain this sample size. Explain how number of subjects needed to answer the research question was determined.**

2000 households will be recruited into each study arm (intermittent vs. continuous water delivery), with a total of 4000 households. With one adult participants in each enrolled household and assuming an average of two children under the age of five per household, this will result in 12,000 participants. If there are more than two children under five in a household, all of them will be recruited into the study. Each house will be visited once every three months for the duration of a year. This will yield 80% power to detect our hypothesized health impact in two different income strata, using a one-sided alpha of 5% (assuming 10% loss to follow-up and adjusting for clustering).

An additional 700 households will be contacted solely for water quality testing, and will not participate in the full health study. This number was determined based on the availability of water quality testing equipment to the investigators. In these households, the household head will be recruited to provide a water sample from their tap and storage containers to the investigators. In addition to providing water quality samples, these participants will be asked to answer questions from a brief sanitary survey about their water collection practices.

There will be a total of 12,700 participants (4000 households with one adult and an average of two children per household for the health study, and 700 additional individuals for water quality testing).

**c) If any proposed subjects are children/minors, prisoners, pregnant women, those with physical or cognitive impairments, or others who are considered vulnerable to coercion or undue influence, state rationale for their involvement.**

Data on the occurrence of diarrhea and highly credible gastrointestinal illness (HCGI) will be collected on children under the age of five as this age group is particularly vulnerable to and suffers high morbidity and mortality from those illnesses, with almost 2 million annual deaths, 85% of them in young children in developing countries. Anthropometric measures will also be taken on the children as persistent diarrheal illness can lead to stunted growth. The proposed evaluation of continuous water delivery will fill an important information gap on whether this intervention leads to improvements in child health and the findings can be applied to develop water-related interventions that will effectively reduce childhood

---

**Protocol Title:** Impact Evaluation for Continuous Water Delivery in Hubli-Dharwad, India  
**Protocol Status:** APPROVED  
**Date Submitted:** 12/08/2010  
**Approval Period:** 12/20/2010-06/07/2011  
**Important Note:** This Print View may not reflect all comments and contingencies for approval. Please check the comments section of the online protocol. Questions that appear to not have been answered may not have been required for this submission. Please see the system application for more details.

mortality from diarrheal illnesses across the developing world.

The information on the occurrence of diarrhea and HCGI will be obtained from the primary caretaker of the children, and not the children themselves. Anthropometric measurements (weight, height, head and upper arm circumference) will be taken on the children.

